##### Clinician Perceptions of Practice

To obtain ICU clinician feedback on preparing transfer summaries (see Table 1), we will analyze survey data collected pre- and postimplementation of the e-transfer tool. Our survey was adapted from a validated survey used to assess physician perceptions using a similar transfer tool [39,55]. We disseminated it via paper and online to ICU NPs and residents. The time between the two dissemination periods was over a year, making response bias unlikely. Participants were asked to rate their experience completing their last transfer summary on seven criteria: process (ie, understood what to include and how to accomplish this), workload (ie, completing was manageable within routine ICU workflow), effectiveness (ie, able to communicate all relevant information clearly and logically), revision (ie, able to easily edit and update the transfer summary with new information), timeliness (ie, able to complete by the time the patient is transferred from ICU), satisfaction (ie, summary was of high quality), and confidence that the accepting medical team will understand the patient care plan. Participants were also asked to estimate how long it took them, in minutes, to complete their last ICU transfer summary.

#### Sample Size Calculations

Sample size calculations were based on the cluster-specific pre-post study design. Based on our pilot [41,42], we calculated a required sample size of 144 pre- and 144 postimplementation ICU transfer summaries from each hospital to assess our primary outcome. This will be sufficient to detect an absolute difference in our primary outcome of 15% for each hospital with 82% power and an α value of 5% based on a baseline proportion of 20%; we observed a change in our pilot from 23% to 83%. A random sample of 24 ICU patients per hospital per month, over 6 months pre- and 6 months postimplementation, will facilitate secondary analyses, which accommodate the possibility of secular trends. The study biostatistician (AS) determined the random sample by assigning computer-generated random numbers to the complete list of patients transferred from each ICU within the study period, which was extracted by a data analyst with the critical care analytics system (see Figure 2). The study biostatistician was blinded to the method used to create the summary at the time of randomization.

To collect clinician ratings of the transfer summary quality, we calculated requiring 64 summaries preimplementation (ie, 16 per hospital × 4 hospitals = 64) and 64 summaries postimplementation (ie, 16 per hospital × 4 hospitals = 64), which will be sampled from aforementioned summaries, to detect an absolute difference in means as small as 0.5, assuming an SD of 1, with 80% power and an α value of 5%. The same patient cases will be used to assess for suspected post-ICU adverse events.

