## Methods

### Setting

This evaluation study takes place in four acute care hospitals servicing a single city, Calgary, Alberta, Canada, which has a referral population of approximately 1.7 million. Three of the four hospitals are academic hospitals operating a combined 56 adult medical-surgical ICU beds; the fourth is a nonacademic, community-based hospital operating 10 ICU beds. The annual ICU admission rate across the city approximates 3000 patients. In addition to the CIS hosting the e-transfer tool (ie, Sunrise Clinical Manager), all ICUs also use a dedicated provincial critical care CIS (ie, eCritical MetaVision) and clinical analytics system (ie, eCritical TRACER) that capture key demographic, clinical, health care service, and outcome data for all ICU patients [49]. ICUs are staffed by multidisciplinary teams; those in academic-based hospitals operate with a clinical fellow and 4 to 10 residents working under the supervision of an attending physician. One ICU has an NP. Critical care resident rotation blocks are 4 weeks in duration. The community-based ICU functions with an attending physician and 4 NPs.

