#### Data Analysis

Demographic characteristics pre- and postimplementation for each hospital will be described using medians with IQRs, means with SDs, and frequencies with percentages, as appropriate. The primary outcome will be compared within each hospital pre- and postimplementation using separate logistic regression models for each hospital, with adjustment for the following patient characteristics: age, sex, reason for ICU admission, status on ICU admission (ie, Charlson Comorbidity Index, APACHE II, GCS, and SOFA), therapies received while in ICU (ie, ventilation, vasoactive medications, intermittent hemodialysis, and continuous renal replacement therapy), status on transfer (ie, transfer delay time, transfer decision cancellations, and ICU occupancy), and ICU length of stay. Pooled analyses across all four hospitals will use mixed-effects logistic regression models with a fixed effect for intervention and a fixed effect for time in months, in order to model the underlying secular trend. A fixed effect for patient characteristics will also be used, as noted above, and random effects will be used for hospital and hospital by time to account for intracluster and interperiod correlation. In case of poor model fit or convergence issues due to a limited number of clusters, hospital-level analyses will be considered by aggregating the primary outcome over all summaries in each hospital during each month and using linear regression of the aggregated cluster-period proportions of complete and timely summaries with fixed effects for hospital and time in months. Secondary outcomes will be analyzed as described for the primary outcome, using within-hospital and pooled analyses. Wilcoxon rank-sum tests will be used to compare ICU and hospital length of stay, and log-rank tests will be used to compare time from ICU discharge to hospital mortality.

Open-ended comments collected through clinician surveys will be analyzed according to standard practices of qualitative textual analysis.

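### The 82% power per hospital assumes independent summaries, and the per-hospital logistic models carry no term for the hospital-by-time correlation that the pooled model allows for

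*Protocol article*

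**What the plan says.** The Sample Size Calculations section opens with "Sample size calculations were based on the cluster-specific pre-post study design". It arrives at "144 pre- and 144 postimplementation ICU transfer summaries from each hospital", takes a baseline of 20% and a 5% α, and concludes: "This will be sufficient to detect an absolute difference in our primary outcome of 15% for each hospital with 82% power". Sampling is 24 patients per hospital per month for 6 months on each side of implementation. The pilot change is given as 23% to 83%.

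The Data Analysis section compares the primary outcome within each hospital by a separate logistic regression. The only adjustment named is for patient-level characteristics, a list that includes transfer delay and ICU occupancy. For the pooled analysis, the same section adds a fixed effect for month and says "random effects will be used for hospital and hospital by time to account for intracluster and interperiod correlation". Secondary outcomes follow the same within-hospital and pooled scheme.

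The Setting section describes who works in the units. The academic ICUs have a fellow and 4 to 10 residents, and "Critical care resident rotation blocks are 4 weeks in duration". At the fourth site, "The community-based ICU functions with an attending physician and 4 NPs". The Participants section identifies residents and NPs as the authors of most summaries.

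**The concern.** The primary outcome depends on what an author does: whether four elements were written down and whether the summary was ready when the patient left. Dictation stayed available after implementation, so use of the tool also depends on the author. Summaries from the same rotation block share a small group of authors and can be expected to resemble one another.

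The pooled model has two random components. The hospital effect is constant within a hospital and drops out of its own before-after contrast. The hospital-by-time effect does not: the six months before and the six months after each carry their own deviations, and these add to the variance of the difference. The per-hospital models treat the same 288 summaries as independent.

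Two things are at stake. The stated power would be optimistic at the 15-point target. More importantly, each hospital's confidence interval would be too narrow and its nominal 5% test would reject too often. The same applies to the secondary outcomes put through these models.

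**Working it through.** **Inputs from the protocol article.** n = 144 per period per hospital; p1 = 0.20; p2 = 0.35; α = 0.05 (taken as two-sided, which reproduces the stated power); m = 24 summaries per hospital-month; 6 + 6 months.

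**Assumed input.** The documents give no ICC, so a hospital-month ICC (ρ) of 0.005 to 0.05 is used as a range.

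**1. Reproducing 82%.** With mean proportion 0.275:
- Standard error under the null = √(2 × 0.275 × 0.725 / 144) = 0.0526
- Standard error under the alternative = √((0.20 × 0.80 + 0.35 × 0.65) / 144) = 0.0519
- Power = Φ((0.15 − 1.96 × 0.0526) / 0.0519) = 81.7%

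The unpooled variant gives 82.4% and the arcsine variant 82.0%. The stated figure is therefore the independent-observations figure.

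**2. Allowing for hospital-month correlation.** Design effect DE = 1 + (24 − 1)ρ; effective n = 144 / DE, put into the same power formula. An ordinary test has true type I error 2 × (1 − Φ(1.96 / √DE)), and its interval has 1/√DE of the correct width.

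| ρ (assumed) | DE | Effective n | Power for 15 points | Difference detectable at 82% power | True type I error of ordinary test | Interval width, share of correct |
|---|---|---|---|---|---|---|
| 0 | 1.00 | 144 | 81.7% | 15.1 points | 5.0% | 100% |
| 0.005 | 1.12 | 129 | 77% | 16.0 | 6.3% | 95% |
| 0.01 | 1.23 | 117 | 73% | 16.9 | 7.7% | 90% |
| 0.02 | 1.46 | 99 | 66% | 18.5 | 10.5% | 83% |
| 0.05 | 2.15 | 67 | 49% | 22.8 | 18.1% | 68% |

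An ICC of about 0.002 is enough to bring power below 80%.

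**3. Simulation check.** Beta-binomial months, 6 + 6 months of 24 summaries, 40,000 runs, unadjusted log-odds Wald test. Type I error was 7.5%, 10.1% and 17.8% at ρ = 0.01, 0.02 and 0.05, close to the formula. The ordinary test's own rejection rate at 20% v 35% stays at 79%, 77% and 73%, but only because it also rejects too often under the null.

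**4. Clustering by author instead of month.** Six months is about 26 / 4 = 6.5 blocks. With 4 to 10 residents per block there are 26 to 65 resident slots per period, hence 144 / 65 = 2.2 to 144 / 26 = 5.5 sampled summaries each, if residents write them all and none returns. Counting one block per month and 4 residents gives 24 / 4 = 6. With an assumed author ICC of 0.1, DE = 1 + (2.2 − 1) × 0.1 = 1.12 up to 1 + (6 − 1) × 0.1 = 1.50, and power runs from 77% down to 65%.

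**5. Power of a valid monthly comparison.** A t-test of 6 v 6 monthly proportions has 10 degrees of freedom (critical value 2.23). For 15 points its power is 74% at ρ = 0, 69% at 0.005, 65% at 0.01, 58% at 0.02 and 43% at 0.05. In simulation its type I error stayed at 4.8 to 5.1%.

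**6. Pilot-sized effect.** For 23% v 83%, power is essentially 100% even at ρ = 0.10 (DE 3.30, effective n 44).

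**The case against.** The strongest reply is that nothing was miscalculated: the stated inputs give the stated output. That is right. A reader might infer an arithmetic error, but the issue is the independence assumption behind the figure. Nor does the point rest on a missing ICC, which a condensed article could leave to a fuller document. It rests on the printed 82% leaving no room for correlation.

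Second, every loss shown depends on an assumed ICC. The pooled model provides for correlation but does not say how large it is. This stands. The direction follows for any positive hospital-by-time correlation; the size cannot be fixed from the documents. Adjustment for case mix, transfer delay and ICU occupancy may also absorb some month-to-month variation.

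Third, a reader might infer that all four hospitals are affected alike. The documents do not support that. Rotation is described only for residents. At the community site the same NPs may write in both periods, and part of any author effect then cancels.

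Fourth, a reader might conclude that the trial is underpowered. The target is 15 points against a pilot change of 60, so it is not underpowered for an effect of that order. Sampling is also complete, so a restated power changes no recruitment decision. Both points stand, and they move the weight from power to the validity of the within-hospital intervals.

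The pooled model, with its monthly-aggregate fallback, does handle the correlation, but only for the pooled estimate. It does not correct the hospital-specific results.

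**Conclusion.** The point holds in limited form. The 82% is the power for 288 independent summaries, while the plan's own pooled model allows for a hospital-by-time component that survives the within-hospital contrast and is absent from the per-hospital models. If that component is positive, those models understate standard errors. This is most plausible at the three academic sites and less clear at the NP-staffed site.

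Under assumed hospital-month ICCs of 0.005 to 0.05, power at 15 points falls to between 77% and 49%, and the nominal 5% error becomes about 6% to 18%. These are illustrations over an assumed range, not estimates. Confidence is high in the direction and low in the size. The consequence that matters is overconfident hospital-specific inference, above all for secondary outcomes, where no pilot-sized margin is assured.

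**What to change.** In the within-hospital models, add a random effect for calendar month or 4-week block, or compare the monthly proportions with a t reference on 10 degrees of freedom. The plan already foresees monthly aggregation as a fallback for the pooled analysis, and the transfer dates needed are being collected.

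Restate per-hospital power, or the detectable difference, as a range over stated ICCs, and make it match the analysis chosen. For the monthly t-test that is about 74% at ICC 0, 69% at 0.005, 65% at 0.01 and 58% at 0.02. The design-effect figures (77%, 73% and 66% at 0.005, 0.01 and 0.02) should not be quoted for that test.

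Use an author random effect only if author identity is retained. It is not among the listed data items, and the Data Collection overview says clinician identifiers are being removed from clinical documents where feasible.

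The cost is wider intervals and a less favourable stated power. The monthly t-test also gives up some power even without correlation (74% against 82%). No additional patients or abstraction are needed for the month or block options.

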#### Outcome Measures

##### Overview

The primary outcome of interest is a binary composite measure of two conditions: information presence and availability (see Table 1). In the first condition, the presence of four essential information elements in the transfer summary—goals of care designation, diagnosis, list of active issues on transfer, and medications to continue on transfer—will be assessed and recorded as *yes* or *no*. All four elements must be present to be recorded as *yes*. In the second condition, the availability of the transfer summary to the accepting clinicians at the time of patient transfer from the ICU will be recorded as *yes* or *no*. Transfer summaries that meet these two conditions will be coded as *present*; those that do not will be coded as *absent*.

Secondary outcomes of interest fall into three main domains (see Table 1): (1) transfer summary quality (ie, completeness, timeliness, and clinician ratings), (2) patient outcomes (ie, post-ICU rapid response activation, cardiac arrest, adverse events, and ICU readmission), and (3) clinician perceptions. The rate of use of the e-transfer tool will also be measured by extracting the type of method—dictation or tool—used to prepare the medical summary for each patient transferred from the ICU during the study period.

**Table 1 table1:** Evaluation outcome measures.

Domain and outcome		Outcome description
Primary outcome—binary (present or absent) composite measure of two conditions: information presence and availability (both conditions need to be met)		Presence of four essential information elements: Goals of care Diagnosis Problem issues on transfer Medications to continue on transfer Completed transfer summary available to patient care unit (PCU) at the time of patient’s transfer out of the intensive care unit (ICU)

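### The 80% power for clinician ratings fits a pooled pre-post comparison with no month term; under the month-adjusted pooled model that the plan prescribes it is about 30–50%

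*Protocol article*

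**What the plan says.** Under Sample Size Calculations, the protocol article asks for "64 summaries preimplementation (ie, 16 per hospital × 4 hospitals = 64") and "64 summaries postimplementation (ie, 16 per hospital × 4 hospitals = 64"), chosen "to detect an absolute difference in means as small as 0.5, assuming an SD of 1, with 80% power" and 5% alpha. No hospital, time or covariate term is mentioned for this calculation.

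The overview of outcome measures places ratings among the secondary outcomes, in the domain "1) transfer summary quality (ie, completeness, timeliness, and clinician ratings").

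Data Analysis then states: "Secondary outcomes will be analyzed as described for the primary outcome, using within-hospital and pooled analyses". The primary outcome has two analyses:
- Within hospital, "using separate logistic regression models for each hospital, with adjustment for the following patient characteristics".
- Pooled, a mixed model with fixed effects for intervention and for time in months, the same patient characteristics, and random effects for hospital and hospital by time.

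Only length of stay and time to in-hospital death are given other tests. The plan names no rating comparison that omits both the month term and the split by hospital.

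**The concern.** The article states a power and an analysis for the same outcome, and the two do not belong together. The go-live dates are two months apart and each hospital contributes six months either side of its own date. Later calendar months are therefore mostly post-implementation months, and a model that estimates both a monthly trend and an intervention effect has limited information to separate them. The 64 + 64 calculation takes no account of this.

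At stake is how a null result would be read. Someone relying on the stated 80% would take a non-significant month-adjusted result as fair evidence against a half-point improvement. If the real power is below one half, such a result is more likely than not even when the improvement exists.

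**Working it through.** **Inputs from the article.** Difference 0.5, SD 1, 64 v 64 in total, 16 v 16 per hospital, alpha 5% (taken as two-sided, which reproduces the figure). Four hospitals, one going live every 2 months, 6 months before and 6 after at each.

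**Assumptions, not in the article.** The 16 summaries per hospital and period are spread evenly over 6 months (16/6 per hospital-month). A linear model is used for the 7-point rating. The SD of 1 is the total SD. The hospital ICC is 0–0.20 and the hospital-month ICC 0–0.05, each as a share of total variance. Covariates explain nothing.

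**1. The stated figure.** SE = √(2/64) = 0.1768. Power = Φ(0.5/0.1768 − 1.96) = Φ(0.868) = 80.7%; the noncentral t with 126 df gives 80.1%. The required number is 63 per period. The 80% reproduces.

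**2. Within one hospital.** SE = √(2/16) = 0.3536. Power = Φ(1.414 − 1.96) = 29.3%; the t version with 30 df gives 27.8%. The difference detectable with 80% power is 2.80 × 0.3536 = 0.99 points.

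**3. Why the month term costs so much.** Take month as linear. Within one hospital's 12 months, month has variance (12² − 1)/12 = 11.92. The post-implementation indicator has variance 0.25. Mean month differs by 6 between periods, so the covariance is 6 × 0.25 = 1.5. Across hospitals the stagger (0, 2, 4, 6 months) adds variance 5.
- No hospital effect: r² = 1.5²/(16.92 × 0.25) = 0.532, so the variance is multiplied by 1/(1 − 0.532) = 2.14.
- Hospital effects fully fixed: r² = 1.5²/(11.92 × 0.25) = 0.755, so the variance is multiplied by 4.09.

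**4. The pooled model with a random hospital effect.** This uses the generalised least squares variance of the intervention effect on the 4 × 12 hospital-months, over the assumed ICC ranges. Power = Φ(0.5/SE − 1.96); detectable difference = 2.80 × SE.

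| Pooled model | SE | Power for 0.5 | Detectable at 80% |
|---|---|---|---|
| Random hospital, no month | 0.158–0.184 | 78–89% | 0.44–0.52 |
| Random hospital, linear month | 0.258–0.315 | 35–49% | 0.72–0.88 |
| Random hospital, month as categories | 0.274–0.338 | 32–45% | 0.77–0.95 |

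With fixed hospital effects and no month term, the SE is again 0.1768 and power 80.7%. Adjusting for hospital is therefore not what loses the power; the month term is.

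**5. Could covariates restore it?** In the most favourable month-adjusted case (SE 0.2584), they would have to explain 1 − (0.5/2.80)²/0.2584² = 52% of the rating variance. Within one hospital the figure is 75%. Neither allows for lost degrees of freedom.

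**The case against.** The strongest reply is that the sample-size arithmetic is right and that the sentence on secondary outcomes is condensed. The primary models are logistic, ratings are 7-point scores, and Table 1 summarises them by median and IQR, so the sentence cannot apply word for word. A fuller plan may specify the rating model. This stands in part: the link function is open. But replacing logistic with linear regression removes neither the month term nor the split by hospital, and the article exempts only length of stay and mortality.

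Second, the article claims power within each hospital for the primary outcome only. For ratings it adds four hospitals to reach 64. This stands. The 28% contradicts no stated claim and matters only for interpretation.

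Third, the month-adjusted figures depend on ICCs that the article does not give. That is why a range is shown; no value in it reaches 50%.

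Fourth, month adjustment guards against secular drift, which the article says its monthly sampling is meant to accommodate. That also stands, and nothing here argues for removing the term.

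**Conclusion.** The point holds as a mismatch between the stated power and the prescribed analysis. The 80% belongs to a pooled pre-post comparison without a month term. Under the pooled model with month and random hospital effects, power for 0.5 points is about 30–50% and the detectable difference about 0.7–0.95 points, under the assumptions listed above.

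A reader might infer more than the article supports:
- That the calculation is wrong, or valid only for an unadjusted comparison. It reproduces, and hospital effects leave it essentially intact.
- That pooled power falls to 25–29%. Those values need fixed hospital effects, which the article names only for a fallback analysis of aggregated primary-outcome proportions.
- That correlation among summaries scored by the same clinician makes matters worse. The number of raters and their allocation are not given, so this cannot be quantified and is not in the figures.
- That the primary outcome is affected. Its power is stated for each hospital, and its within-hospital comparison has no month term.

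This concerns one secondary outcome, and correcting it is a matter of reporting rather than design.

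**What to change.** In Sample Size Calculations, say that the 80% applies to the pooled pre-post comparison of ratings without a month term. Beside it, give the power (about 30–50%) or the detectable difference (about 0.7–0.95 points) for the month-adjusted pooled model in Data Analysis, together with the assumed ICC range. Add that the within-hospital rating comparisons are not powered for 0.5 points, so that a non-significant result is not read as no difference.

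This needs no new data and no change of analysis; the cost is a less favourable stated figure. Making the month-adjusted model a sensitivity analysis, or showing per-hospital ratings only descriptively, would be a further choice for the investigators. The first leaves the main rating result exposed to drift, so neither is required to settle this point.

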## Introduction

### Background

Complete and timely communication between health care providers is integral to seamless transitions in care [1-3]. The transfer of critically ill patients from the intensive care unit (ICU) to another patient care unit (PCU) is a particularly vulnerable period in patient care, due to the high acuity of patients [4-6] as well as the number of health care providers involved and their professional diversity [7-10]. The movement of patients between units requires a high degree of collaboration, with verbal and written communication between health care providers [1-3] as well as patients and families [1,11-13]. Suboptimal communication during transitions can have profound implications for patients, families, and the health care system [14-16], including increased risk of preventable medical errors, adverse events, redundant testing, readmissions, and dissatisfaction with the quality of care [17-24].

An ICU transfer summary is a clinical document that ICU physicians and nurse practitioners (NPs) often prepare to describe a patient’s stay in the ICU, including active and resolved health issues and the current care plan. The transfer summary is intended to support verbal communication between transferring and accepting medical teams and should provide sufficient detail to serve as a stand-alone communication [25]. Complete and timely exchanges of patient care information during transitions in care are critical, not only for immediate continuity of care but also for efficient coordination of future care [26,27]. As such, the transfer summary should be easily accessible to inpatient and outpatient health care providers as part of the patient’s permanent health care record.

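### A patient with no transfer summary cannot enter the adverse-event sample and has no timeliness value, although patients were sampled whether or not they had a summary

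*Protocol article*

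**What the plan says.** Under Sample Size Calculations the sample is counted in two ways. The requirement is in documents: "we calculated a required sample size of 144 pre- and 144 postimplementation ICU transfer summaries from each hospital to assess our primary outcome". The draw is in people: "A random sample of 24 ICU patients per hospital per month, over 6 months pre- and 6 months postimplementation". Random numbers were assigned to everyone on the ICU transfer list for the study period. None of the four criteria under Participants requires a summary.

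For the clinician ratings, 16 summaries per hospital in each period (64 pre, 64 post) are needed, "which will be sampled from aforementioned summaries". The next sentence but one adds: "The same patient cases will be used to assess for suspected post-ICU adverse events". Under Patient Outcomes, adverse events are found by reviewing the ward progress notes for the 3 days after transfer, a source that does not involve the summary.

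Timeliness of Information takes the gap in hours between transfer and the time the document was transcribed (dictation) or last updated (tool).

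For the primary outcome, the Overview of Outcome Measures says "Transfer summaries that meet these two conditions will be coded as" present, and the others as absent. The Background calls the summary "a clinical document that ICU physicians and nurse practitioners (NPs) often prepare".

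**The concern.** The sampling unit is the patient, but two secondary comparisons are restricted, by the way they are defined, to patients for whom a summary was prepared. That is an event after the start of the intervention, and the tool may affect it. Dictation runs through a voice file, transcription, editing and approval. The tool opens a document in the record that can be edited throughout the stay, and its use is backed by education, point-of-care support, and audit and feedback. Selecting on a result of the intervention can make the pre and post groups non-comparable even when the original patient samples are comparable.

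For adverse events the restriction has no practical reason, because the chart review needs only progress notes. For timeliness, a summary that never appears is the extreme case of a late one, yet it yields no hours and so leaves the comparison.

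**Working it through.** **1. The plan's own figures.** 24 patients × 6 months = 144 per hospital and period; 16 × 4 hospitals = 64 per period. The plan expects to "detect an absolute difference in our primary outcome of 15% for each hospital with 82% power", from a baseline of 20%, so 20% against 35%. With n = 144 per period and two-sided α of 5% (sidedness is assumed):

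power = Φ{[0.15 − 1.96 × √(2 × 0.275 × 0.725 / 144)] / √[(0.20 × 0.80 + 0.35 × 0.65) / 144]} = Φ[(0.150 − 0.103) / 0.0519] = 81.7%.

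This agrees with the stated 82%. For the ratings (difference 0.5, SD 1), 64 per period gives 80.1% power by t-test, as stated. The calculations are sound, and the primary one holds if all 144 sampled patients are analysed.

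**2. What happens to a sampled patient with no summary.**

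| Outcome | Depends on a summary? | Result as written |
|---|---|---|
| Adverse events (64 + 64) | Yes, through the draw only | Cannot be selected |
| Timeliness | Yes, through the time stamp | No value |
| Clinician ratings | Yes, by nature | Not rated, unavoidably |
| Primary outcome, completeness | Worded per summary | No explicit rule; could be coded absent and 0 of 8 |
| Readmission, rapid response, cardiac arrest, length of stay, mortality | No | Unaffected |

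The first two rows are fixed by the text.

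**3. Adverse events (all inputs assumed; the documents give none).** Let r be the event rate with a summary, k × r the rate without one, and m the share without one, preimplementation only. Restricting to patients with a summary lowers the preimplementation rate by r × (k − 1) × m.

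- r = 10%, k = 1.5, m = 5%: 0.10 × 0.5 × 0.05 = 0.25 points, about 0.3.
- r = 20%, k = 2, m = 20%: 0.20 × 1 × 0.20 = 4 points.

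The standard error of a difference with 64 per period is √[2r(1 − r)/64]: 5.3 points at r = 10% and 7.1 points at r = 20%.

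**4. Primary outcome, if such patients were dropped (an illustration, not a stated rule).** Take 20% and 35% as the rates in all patients, with no summary counted as absent. The rate among existing summaries is the all-patient rate / (1 − share without one).

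| Assumed share without (pre/post) | Pre | Post | Difference |
|---|---|---|---|
| 5% / 1% | 0.20/0.95 = 21.1% | 0.35/0.99 = 35.4% | 14.3 points |
| 10% / 2% | 0.20/0.90 = 22.2% | 0.35/0.98 = 35.7% | 13.5 points |
| 15% / 3% | 0.20/0.85 = 23.5% | 0.35/0.97 = 36.1% | 12.6 points |
| 5% / 5% | 0.20/0.95 = 21.1% | 0.35/0.95 = 36.8% | 15.8 points |

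With none missing post, power with the reduced n falls to 74% at 5% missing pre (13.9 points) and 65% at 10% (12.8 points). With 5% missing in both periods it stays at about 82%. The loss therefore comes from the imbalance between periods, not from missing summaries as such.

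**The case against.** A reader might infer that patients with no summary also drop out of the primary outcome and completeness. The documents do not say so. Availability at transfer is recorded as yes or no and each information element as 1 or 0, so a patient with no document can be coded no and 0 without any new rule. The abstraction form, an appendix not shown here, may already do this. That part of the objection stands, and confirmation is all that is needed there.

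A reader might also infer that the share without a summary is higher before implementation, and that the worst handovers are therefore hidden from one period. No figure supports this. The word often in the Background sits in a general definition and is not a local completion rate. The Overview of Outcome Measures speaks of a preparation method, dictation or tool, for each transferred patient, which presumes that a summary exists. Dictation stayed available after implementation. If nearly every patient has a summary, the practical effect is nil. Nor do the documents show that patients without a summary have more adverse events.

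Finally, the assumed shifts in step 3 lie within sampling error at 64 per period, and the shifts in the first three rows of step 4 would understate the tool's benefit. This is also fair, and it limits the weight of the point.

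The objection does not remove the two stated rules. The adverse-event cases are tied to rated summaries although the review does not need them, and timeliness has no value when no document exists. These are sampling and outcome definitions in the article itself, not details left to an analysis plan.

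**Conclusion.** The point holds for adverse events and timeliness. In both, the comparison as defined is confined to patients with a summary, although the patients were sampled without that condition. It does not hold as a claim that the primary outcome or completeness excludes such patients, that the ratings are at fault for needing a document, or that a difference between periods has been shown.

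The size is unknown because the documents report no no-summary share in either period. Under the assumptions in step 3, the preimplementation adverse-event rate would be lowered by 0.3 to 4 points. The primary-outcome figures of 14.3 to 12.6 points rest on an assumed five-to-one ratio of shares between periods and apply only if such patients were dropped. The change is worth making because it is cheap, and because the researchers abstracting the summaries are not blinded to period, so a missing document should not be left to judgement case by case.

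**What to change.** - **Adverse events:** draw the 16 pre and 16 post cases per hospital from all sampled patients, whether or not a summary exists. Keep only the ratings restricted to existing summaries.
- **Timeliness:** keep patients with no summary in the comparison as not available, for example censored at hospital discharge or ranked worst, and state which.
- **Unit:** confirm that the sampled patient is the unit, with no summary coded as absent on the primary outcome and 0 of 8 on completeness. Align the wording under Outcome Measures, Sample Size Calculations and the fallback analysis in Data Analysis, which aggregates over summaries.
- **Reporting:** give the number of sampled patients with no summary by hospital and period.

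The cost is wording plus a few replaced or added chart reviews. At the assumed shares of 5% to 15% pre and 1% to 3% post, about 3 to 10 of the 64 preimplementation cases (64 × 0.05 = 3.2; 64 × 0.15 = 9.6) and about 1 to 2 of the 64 postimplementation cases (64 × 0.01 = 0.6; 64 × 0.03 = 1.9) would have no summary. The small downside is that the rated cases and the adverse-event cases no longer overlap completely. Abstraction was already under way when the article appeared, so the rule is best fixed before the data are analysed.
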